### Power calculations

Power calculations were conducted using PASS 2019, v19.0.6 (NCSS, Kaysville, Utah, USA), accounting for the cluster-randomised design. Whilst hypotheses for the two primary outcomes (urinary pesticides and dietary diversity) were independent, in order to be conservative, a Bonferroni correction was applied (0.05/2, which is the number of primary outcomes) resulting in a two-sided alpha level of 0.025. It is expected that approximately 20% of the baseline sample will be loss-to-follow-up at 12 months. Two previous surveys in Andhra Pradesh by study team members had much lower loss to follow-up rates [2% from 2019 to 2020 in the SHEFS (Sustainable and Healthy Food Systems) nutrition survey (unpublished) and 10% for the mWellcare trial [104] but a higher rate was anticipated for the BLOOM study due to COVID-19.

Power for the primary outcomes is given in Table 5, which summarises the minimal detectable difference in mean levels associated with 80% power, a type I error rate alpha of 0.025, an intra-cluster correlation of 0.02, and 20% loss to follow-up. For ∑DAPs power calculations are shown for 150 per arm (a 15% subsample). Results in Table 5 confirm that the study is adequately power to detect a smaller difference than has been previously reported in the literature for these outcomes.

**Table 5 pone.0281677.t005:** Minimum detectable mean difference, with 80% power, alpha = 0.025, and intra-cluster correlation of 0.02.

	Standard Deviation for Mean Change in Outcome	Sample Size per Group	Minimum Detectable Mean Difference	Previous Study Estimate (95% Confidence Interval)
Change in mean ∑DAPs, adult men	111 μmol/l*	150	39.6 μmol/l (~55% of estimated baseline levels*)	-88% (not reported)^†^
Change in mean ∑DAPs, adult women	111 μmol/l*	150	39.6 μmol/l (~55% of estimated baseline levels*)	-88% (not reported)^†^
Change in mean ∑DAPs, children	17.3 nmol/l^‡^	150	6.17 nmol/l (~9.7% of estimated baseline levels^‡^)	-42.7% (-76.3–38.7)^‡^ -39.9% (-58.6, -12.6)^§^
Change in mean dietary diversity score, adult women	1.57^¶^	1000	0.29	0.36 (0.03–0.69)^¶^
Change in mean dietary diversity score, children	1.40^#^	1000	0.26	0.39 (0.13–0.64)^#^

* From an observational study of adult agricultural labourers in North Carolina [105].

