^†^ From an observational cross-sectional study comparing organic and conventional vegetable farmers in Thailand [106]. Difference is for urinary levels of 3,5,6-trichloro-2-pyridinol, a metabolite of chlorpyrifos, a specific organophosphate.

^‡^ Percent reduction in ∑DAPs reported for children under 4 years old participating in a home-based educational intervention to reduce take-home pesticides by agricultural labourers in California, USA [107]. Change is from baseline to 3 months.

^§^ Percent reduction in ∑DAPs reported for children 3–6 years old living in urban or agricultural communities in California, USA, who were fed organic food for 4 days [108]. Change is between the control period (9 days) and intervention period (7 days).

^¶^ From a cluster-randomised controlled trial of a nutrition-sensitive agroecology intervention in Tanzania for which a secondary outcome was minimum dietary diversity among women [30]. The estimates used in these power calculations are from the 12-month follow-up visit. Dietary diversity was assessed using the FAO’s minimum dietary diversity score for women, the same as BLOOM. The standard deviation for mean change in outcome is estimated from the control group.

^#^ From a cluster-randomised controlled trial of a nutrition-sensitive agroecology intervention in Tanzania for which the primary outcome was dietary diversity among children aged <1 year at baseline [30]. The estimates used in these power calculations are from the 12-month follow-up visit. Dietary diversity was assessed using the older version of the WHO’s minimum dietary diversity score that did not include breastmilk and so was out of a total of seven food groups instead of eight. The standard deviation for mean change in outcome is estimated from the control group.

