### Statistical analysis plan

The main analyses will be intent-to-treat, i.e., participants will be analysed as assigned, regardless of their fidelity to APCNF practices. Herein the analyses for primary outcomes are described. Analyses for secondary outcomes will be analogous. Separate models will be run for each of the primary outcomes. All primary outcomes are continuous. General estimating equation (GEE) models with robust standard errors will be used to account for within-participant correlations [111]. Models will account for clustering within villages. The models will take the form of:

$$Y_{i,t}=\beta_{0}+\beta_{1}Group+\beta_{2}Time+\beta_{3}Group*Time+\beta_{4}District+\varepsilon_{i,t}$$
(1)

where group is APCNF or control, time is baseline or 12 months, and district is Kurnool or Visakhapatnam (to account for randomisation stratification). β_3_ represents the difference in the change from baseline to 12 months in the APCNF group and the change from baseline to 12 months in the control group (e.g., difference in difference).

We will evaluate whether missing data are differential between groups using t-tests. We will assume missing data to be missing at random and conduct a complete-case analysis. Inverse probability weighting will be used to account for loss to follow-up. We will run adjusted models to address potential baseline imbalance across clusters and improve precision. Covariates will be selected based on p-values for differences across groups.

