## Discussion

### Study implications

The BLOOM study will provide robust evidence of the impact of a large-scale transformational government-implemented agroecology programme on pesticide exposure and dietary diversity in agricultural households in rural Andhra Pradesh, India. It will also provide the first evidence of the health co-benefits of adopting agroecology, inclusive of malnourishment and common chronic diseases including type 2 diabetes and kidney disease, as well as early child development. In working closely with the government organisation responsible for implementation from the outset of the study, the study team will help to ensure that the study’s outcomes are priorities for the government and that the findings are rapidly disseminated and integrated into agriculture and public health policy in India. Whilst fully recognising that APCNF is unlikely to be the best solution in all contexts, this research study will provide evidence regarding its effectiveness in India with direct generalisation to other countries in South Asia and Africa considering adopting the approach [e.g., Nepal and Rwanda [113]].

This will be the first evaluation of a programme aimed at eliminating pesticide exposure among farmers in a low- or middle-income country to measure biomarkers of pesticide exposure. All previous studies in these contexts have relied on self-reported pesticide use. For example, our cross-sectional pilot study in Kurnool district, Andhra Pradesh, conducted between August and November 2020 found that APCNF farmers were 34% less likely to use synthetic pesticides compared to conventional farmers [12]. One cross-sectional comparison of n = 8 pesticide-free vegetable farmers and n = 11 conventional vegetable farmers in Chiang Mai, Thailand, found substantial reductions in urinary pesticide biomarkers [106].

Given that agroecology, including APCNF [114], explicitly promotes the diversification of crops cultivated, and crop diversity is positively associated with dietary diversity [114], one might expect agroecology to have an impact on dietary diversity. However, to the best of our knowledge, only one previous study, in Tanzania, has evaluated the impact of an agroecology programme on dietary diversity, finding significant improvements in child and women’s dietary diversity [30].

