### Study strengths and limitations

The BLOOM study is led by a multi-disciplinary team of researchers and leverages a scientifically rigorous study design, employing cluster randomisation, which will strengthen causal inferences. The research questions were informed through discussions with policymakers and the government implementing agency, and government stakeholders have been involved since its inception. This is a randomised controlled evaluation in four districts of one state in south India and thus will not necessarily be generalizable to all districts in Andhra Pradesh nor all states in India. Nonetheless, these districts are relatively comparable to state- and national-level demographic and health characteristics (Table 2). The primary outcome of ∑DAPs will capture changes in organophosphate pesticides but not all pesticides. Our preliminary findings from Kurnool indicated that organophosphate pesticides were the most commonly reported pesticides used by farmers and the top-selling pesticides at retail shops [12]. However, if no change in ∑DAPs is observed, it will not be possible to make any conclusions about changes in other classes of pesticides such as pyrethroids, carbamates, neonicotinoids, or fungicides. Additional limitations include the use of self-report to assess dietary intake and APCNF fidelity.

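### The adequate-power statement for adult ∑DAPs has no adult ∑DAP benchmark behind it, and the 55% detectable fall becomes about 64% if the stated 20% loss applies to the 150 per arm

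*Protocol article*

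**What the plan says.** The Power calculations section of the protocol article applies a Bonferroni correction, "resulting in a two-sided alpha level of 0.025". It says that Table 5 gives detectable differences for "80% power, a type I error rate alpha of 0.025, an intra-cluster correlation of 0.02, and 20% loss to follow-up". For adult men and for adult women, Table 5 lists an SD of 111 µmol/l, 150 per group, a detectable difference of 39.6 µmol/l (about 55% of estimated baseline) and one earlier estimate, -88%, with its interval not reported. The text concludes that the study is "adequately power to detect a smaller difference than has been previously reported in the literature for these outcomes".

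The footnote to the -88% describes a cross-sectional comparison of organic and conventional farmers and adds: "Difference is for urinary levels of 3,5,6-trichloro-2-pyridinol, a metabolite of chlorpyrifos". Study implications gives the size of that source: "One cross-sectional comparison of n = 8 pesticide-free vegetable farmers and n = 11 conventional vegetable farmers". The same section reports that the pilot "found that APCNF farmers were 34% less likely to use synthetic pesticides compared to conventional farmers".

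Under Statistical analysis plan, "participants will be analysed as assigned, regardless of their fidelity to APCNF practices". Under Government intervention, individual training follows a farmer's own interest and no money is paid for taking part. Table 3 also admits households that only earn agricultural wages.

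**The concern.** The primary outcome is the specific gravity-adjusted sum of six dialkylphosphates. The adult benchmark differs from it in two ways. It is a different analyte, and it contrasts farmers who already use no pesticides with farmers who do, whereas the trial averages over everyone in the sampled households of an intervention village, whether or not they adopt. The power section allows for clustering, loss and multiplicity but states no allowance for partial adoption. A detectable fall below 88% therefore does not show adequate power for the effect that will be estimated.

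The detectable fall itself may also be too favourable, because the ∑DAP and dietary rows of Table 5 appear to treat the 20% loss differently. Two of the six outcome-by-group primary comparisons are affected. If the programme lowers adult exposure by a real but moderate amount, a non-significant result is quite likely, and the stated adequacy would invite readers to take it as absence of effect.

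**Working it through.** **Inputs.** From Table 5: adult SD 111 µmol/l, 150 per arm, detectable difference 39.6 µmol/l (~55%); dietary SDs 1.57 and 1.40, 1000 per arm, detectable differences 0.29 and 0.26; earlier estimates -88% (adults), -42.7% and -39.9% (children). From Power calculations: two-sided alpha 0.025, power 80%, ICC 0.02, loss 20%. From Study design: 40 clusters per arm.

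**Formula.** For n per arm, m = n/40, DE = 1 + (m - 1) × 0.02, SE = SD × √(2 × DE/n). The detectable difference is 3.083 × SE with normal quantiles (2.241 + 0.842), or 3.134 × SE with a t reference on 78 df (80 clusters less 2).

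**1. The printed adult figure.**
- 150 per arm, no clustering: SE = 111 × √(2/150) = 12.82; 3.083 × 12.82 = 39.5.
- 160 per arm (4 per cluster), DE 1.06: SE = 12.78; 3.083 × 12.78 = 39.4.
- 150 per arm, DE 1.055: SE = 13.16; 40.6 (normal) or 41.3 (78 df).

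So 39.6 is reproduced by 150 analysed without clustering, or by 160 analysed with it. Neither takes 20% off 150.

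**2. The dietary rows.**
- 1000 per arm, DE 1.48, 78 df: 0.268 (women) and 0.239 (children). These do not match.
- 800 per arm (1000 less 20%), DE 1.38, 78 df: women 1.57 × √(2.76/800) × 3.134 = 0.289; children 1.40 × √(2.76/800) × 3.134 = 0.258. These match 0.29 and 0.26.

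At the stated alpha and ICC, the dietary rows include the loss.

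**3. The same basis for adult ∑DAPs.** 150 is 15% of 1000, so 150 less 20% is 120: m = 3, DE = 1.04, SE = 111 × √(2.08/120) = 14.61. Detectable difference 3.134 × 14.61 = 45.8 µmol/l. The implied baseline is 39.6/0.55 = 72 µmol/l, so the detectable fall is 45.8/72 = 64%. Power at the printed 39.6 is then 66%.

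**4. If the number is after loss.** 160 per arm gives 39.4 to 40.0 µmol/l (55 to 56%); 150 per arm with clustering and 78 df gives 41.3 µmol/l (57%).

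**5. Adoption needed.** Assume that adopters fall by 88%, and that non-adopters and controls do not change. A 55% average fall needs 0.55/0.88 = 62.5% adoption; a 63.6% fall needs 0.636/0.88 = 72%.

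**6. Power by size of the intention-to-treat fall** (baseline 72, SD 111, alpha 0.025):

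| Fall | µmol/l | 120 per arm, ICC 0.02, 78 df | 150 per arm, ICC 0.02, 78 df | 150 per arm, no clustering, normal |
|---|---|---|---|---|
| 34% | 24.5 | 28% | 34% | 37% |
| 39.9% | 28.7 | 38% | 46% | 50% |
| 42.7% | 30.7 | 43% | 52% | 56% |
| 44% (half adopt, adopters fall 88%) | 31.7 | 46% | 55% | 59% |
| 55% | 39.6 | 66% | 76% | 80% |
| 88% | 63.4 | 98% | 99% | over 99% |

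**The case against.** **The sentence is literally true.** It claims only that a smaller difference than previously reported can be detected; 55% is below 88%, and the footnote names the analyte. A reader might infer that the statement is false. That goes too far. The benchmark is disclosed, and what fails is the step from it to adequate power for an intention-to-treat ∑DAP effect.

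**The pilot proves little either way.** A reader might infer that the trial cannot detect the effect its own pilot found, because 34% is below 55%. The documents do not support this. The pilot figure is a cross-sectional difference in the likelihood of using any synthetic pesticide, by self-report. Continuing users may apply less, so the fall in mean ∑DAPs could exceed 34%; non-adopters and dietary sources could make it smaller. The 34% row is illustrative only.

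**The loss may already be covered.** The plan enrols about 34 × 40 = 1360 households per arm; 15% is 204, and 80% of that is 163, which gives 39.7 µmol/l with ICC 0.02 and 78 df. Urine is collected in up to 12 households per cluster, so 150 assays could be filled from people retained. This stands as a possibility, and the 64% is conditional for that reason. However, Table 5 prints 150 and 1000, not 163 and 1088, and 1088 does not reproduce the dietary rows. Alpha 0.05 with ICC 0.05 and 1000 per arm would also give 0.29 and 0.26, but those inputs contradict the table's own title.

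**Reading of a null result.** Study strengths and limitations says that, if ∑DAPs do not change, "it will not be possible to make any conclusions about changes in other classes of pesticides". A reader might infer that the trial will treat a null as proof of no organophosphate effect. The text does not say so; it is silent on precision in adults. The per-protocol analysis, fidelity indicators, process evaluation and 24-month ∑DAPs will help interpretation, but none raises 12-month intention-to-treat power.

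**Conclusion.** The concern holds for adult men and adult women. No prior adult ∑DAP difference is cited, and the only benchmark is a different metabolite in a small contrast of pesticide-free and conventional farmers. Adequate power for an intention-to-treat adult ∑DAP effect is therefore not established.

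The design has 80% power for a fall of about 64% if the 150 is before loss, or about 55 to 57% if 150 to 160 per arm are assayed after it. Even on the 88% benchmark this requires roughly 63 to 72% adoption. For falls of 40 to 43%, power is about 38 to 56%; those reductions come from children in other settings, and the interval for the larger one includes no change.

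The figures rest on the protocol's SD and ICC, the baseline implied by its 55%, and, for adoption, no change in non-adopters or controls. Table 5's adult arithmetic is not itself at fault. The children's ∑DAP rows are not affected: their detectable fall is about 10% (about 11% at 120 per arm), well below the reductions cited.

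**What to change.** In Power calculations:

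- Withdraw the adequacy statement for adult ∑DAPs and say that no earlier adult ∑DAP estimate is available.
- State whether 150 per arm is before or after loss. Give the detectable intention-to-treat fall as about 64% if before, or about 55 to 57% if 150 to 160 paired assays per arm are guaranteed after loss.
- State that this needs about 63 to 72% adoption even if adopters fall by 88% and non-adopters do not change, and that power is about 38 to 56% for falls of 40 to 43%.
- If a 34% scenario is shown (power about 28 to 37%), mark it as illustrative, because the pilot measured self-reported use.
- Add that a non-significant adult ∑DAP result will be interpreted from its confidence interval and not as evidence of no change in organophosphate exposure.

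The cost is a revised paragraph and a less favourable stated figure; no participants or assays are added. As an option, assaying more of the urine already planned would improve precision. With all 12 households per cluster (480 per arm, or 384 after 20% loss), normal quantiles and ICC 0.02, the detectable fall is about 34 to 37%, at the price of the extra assays.

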### Study design

This study is a community-based, cluster-randomised controlled evaluation with two parallel groups: APCNF (‘intervention’) versus conventional practices (‘control’). A total of 80 clusters will be randomly allocated 1:1 to intervention or control. The study will run for 48 months, including evaluation development and setup; baseline, midline, and endline assessments; intervention implementation (24 months); laboratory measurements of biomarkers; and statistical analysis. The main study assessments will be conducted during monsoon cultivation (July-December) with a brief survey also conducted after the monsoon harvest (January-February). The same random subset of households enroled at baseline from each cluster will be followed at 12 and 24 months post-baseline assessment.

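### The SD behind the child ∑DAPs power row (17.3 nmol/l) does not fit the confidence interval quoted from the same source, so the 9.7% detectable difference is unsupported and much too favourable

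*Protocol article*

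**What the plan says.** All the relevant figures are in the protocol article, under Power calculations and in Table 5.

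- Design inputs: "80% power, a type I error rate alpha of 0.025, an intra-cluster correlation of 0.02, and 20% loss to follow-up", with the Bonferroni step "resulting in a two-sided alpha level of 0.025".
- Sample: "For ∑DAPs power calculations are shown for 150 per arm (a 15% subsample"). Under Study design: "A total of 80 clusters will be randomly allocated 1:1 to intervention or control".
- Child ∑DAPs row: SD of change 17.3 nmol/l and detectable difference "6.17 nmol/l (~9.7% of estimated baseline levels"). Two earlier estimates are listed beside it: -"42.7% (-76.3–38.7"), and -39.9% (-58.6 to -12.6) from a different study.
- Footnote ‡ is attached to the child SD, to the child baseline and to the -42.7% estimate. It describes the source as "Percent reduction in ∑DAPs reported for children under 4 years old participating in a home-based educational intervention", with change measured from baseline to 3 months. It gives no sample size and does not say how 17.3 was obtained.
- Adult ∑DAPs rows: SD 111 μmol/l and detectable difference "39.6 μmol/l (~55% of estimated baseline levels"), set against an earlier estimate of -88%.

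The text before the table concludes that power is adequate for differences smaller than those reported before for these outcomes.

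**The concern.** An estimate's standard error is its individual-level SD divided by a function of the sample size, so with any usable sample it is much smaller than the SD. Here the relation is reversed: the CI quoted from source ‡ implies a standard error larger than the SD attributed to source ‡. One of the two cannot mean what the table says it means.

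Child ∑DAPs at 12 months is a named primary outcome. A reader of Table 5 would conclude that the trial can detect a reduction of about 10% in children, and would carry that expectation to a null result. If 17.3 is really a standard error, the trial's sensitivity in children is several times poorer than stated and may not reach the 40% to 43% reductions cited beside it.

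**Working it through.** **1. Reproduce the stated figure.** Minimum detectable difference (MDD) = (z₀.₉₈₇₅ + z₀.₈₀) × SD × √[(2/n) × (1 + (m − 1) × ICC)], with z-sum 2.241 + 0.842 = 3.083.

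- n = 150, no design effect: 3.083 × 17.3 × √(2/150) = 6.16.
- n = 160 (40 clusters of 4), ICC 0.02: 6.14 (6.16 with a t distribution).
- n = 150, m = 150/40 = 3.75, ICC 0.02 (design effect 1.055): 6.33.

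The stated 6.17 follows from SD 17.3 to within about 2.5%. The calculation is sound, so the question is the input.

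**2. Implied child baseline.** 6.17/0.097 = 63.6 nmol/l (63.3 to 63.9 allowing for rounding). SD/baseline = 17.3/63.6 = 0.272. If the data are roughly lognormal, log-SD = √ln(1 + 0.272²) = 0.267.

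**3. Standard error (SE) implied by the CI.**

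- Log scale: the limits are ratios of 0.237 and 1.387. Their geometric mean is √(0.237 × 1.387) = 0.573, a change of -42.7%, which is the stated point estimate. The arithmetic midpoint is -18.8%. The interval was therefore almost certainly built on the log scale. SE = (ln 1.387 − ln 0.237)/3.92 = (0.327 + 1.440)/3.92 = 0.451.
- Arithmetic reading, for completeness: SE = (38.7 + 76.3)/3.92 = 29.3 percentage points, and 0.293 × 63.6 = 18.7 nmol/l.

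On either scale the SE exceeds the supposed SD (0.451 against 0.267; 18.7 against 17.3).

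**4. Source sample size needed to reconcile them.** For a two-group comparison, n per arm = 2 × (SD/SE)².

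| Reading | Children needed |
|---|---|
| Log, two groups | 2 × (0.267/0.451)² = 0.7 per arm |
| Log, difference in differences, uncorrelated visits | 4 × (0.267/0.451)² = 1.4 per arm |
| Arithmetic, two groups | 2 × (17.3/18.7)² = 1.7 per arm |
| One-group change | 0.35 (log) or 0.86 (arithmetic) |

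No credible study fits any of these.

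**5. Detectable difference if the CI is right.** The source's sample size is not in the article, so it is varied here as an assumption. SD = SE × √(n_source/2). BLOOM has 150 per arm with design effect 1.055, so the multiplier is 3.083 × √(2 × 1.055/150) = 0.366. The detectable reduction is 1 − exp(−0.366 × log-SD) on the log scale, or 0.366 × SD/baseline on the arithmetic scale.

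| Assumed source n per arm | Log-SD | Detectable, log | SD/baseline | Detectable, arithmetic |
|---|---|---|---|---|
| 10 | 1.01 | 31% | 0.66 | 24% |
| 20 | 1.43 | 41% | 0.93 | 34% |
| 30 | 1.75 | 47% | 1.14 | 42% |
| 50 | 2.25 | 56% | 1.47 | 54% |

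The detectable reduction passes 42.7% at about 23 per source arm (log) or 32 (arithmetic). It passes 39.9% at about 19 or 28.

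**6. Comparison within the table.** The adult baseline is 39.6/0.55 = 72, so adult SD/baseline = 111/72 = 1.54, which is 5.7 times the child ratio. If 1.54 applied to children, the MDD would be 55% without a design effect (1.54 × 3.083 × √(2/150)) or 56% with it (0.366 × 1.54).

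**7. Is 150 before or after loss?** 40 clusters × 34 households × 0.8 = 1,088 per arm, tabulated as 1000, and 15% of 1000 is 150. The 150 already reflects the 20% loss, so no further reduction is applied.

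**The case against.** The strongest reply is that the contradiction is not a strict proof. The CI belongs to a ratio, so converting it to 18.7 nmol/l treats a log-scale interval as an arithmetic one, and the article does not say that the percentage was taken against a 63.6 nmol/l baseline. The log-scale comparison turns a raw SD of change into a log-SD by assuming lognormal data. Metabolite values near zero could combine a modest raw SD with a large log-SD. This stands in part: a reader might infer that 17.3 is mathematically impossible, and the article does not establish that. It does establish that both scales, and every design reading tried, point the same way by a wide margin.

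A second reply concerns the adequacy sentence. A reader might infer that it is false for children. The article does not show that: with 10 children per source arm the detectable reduction stays below both cited estimates, and with 20 it is about 41% (log) or 34% (arithmetic), still below 42.7%. It fails only above roughly 20 to 30 per source arm, or if the adult ratio applies. The adult figures come from North Carolina labourers and the child figures from Californian under-4s, so carrying 1.54 across is an assumption.

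Three further limits apply. Cutting the sample to 120 per arm for attrition would count the loss twice. The adult rows, at 55% against a cited -88%, are not affected by this point. The μmol/l and nmol/l labels put the implied baselines about 1,100-fold apart (72 μmol/l against 63.6 nmol/l), which deserves a check, but the percentages do not depend on the labels and this says nothing about 17.3.

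**Conclusion.** The point holds as an unsupported input, not as a calculation error. Table 5 takes from one source an SD of 17.3 nmol/l and a CI whose standard error is larger than that SD (about 0.45 against 0.27 on the log scale, assuming roughly lognormal data). Reconciling them needs fewer than two children per arm. The value 17.3 is the size of a standard error, and the 9.7% figure that rests on it cannot be relied on.

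No single replacement value can be given, because the source's sample size is not in the article. For 10 to 50 children per source arm the detectable reduction is about 31% to 56% (log) or 24% to 54% (arithmetic), roughly 2.5 to 6 times the stated 9.7%. The adequacy sentence is unsupported for children, and false if the source had more than roughly 20 to 30 per arm.

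**What to change.** - Recover the individual-level SD from source ‡, preferably of log ∑DAPs, and state how it was obtained. If only a standard error is available, convert it using the source's sample size.
- Alternatively, estimate the SD blinded from BLOOM's own baseline urine samples. One time point cannot give an SD of change, so state the baseline-to-follow-up correlation that is assumed and show a range for it.
- Recompute the child row at 150 per arm, saying that this is net of loss, and withdraw 9.7%.
- Restate the adequacy sentence for children to match the new figure.
- Check the μmol/l and nmol/l labels in the ∑DAPs rows.

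The cost is a correction to one table row and one sentence. Sampling, follow-up and analysis do not change, but the stated sensitivity in children will be less favourable.
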